**Cointerventions**

**Permissible combination**

According to the diagnosis and treatment program of pneumonia related to infection by the novel coronavirus of the Health Commission (trial version 5), antiviral treatment, nutritional support, maintenance of internal environmental stability and necessary antibiotics can be combined. If the condition requires short-term use of glucocorticoids, it is accurately recorded.

**Prohibited combinations**

Other drugs that regulate the storm of immune factors, such as IL-6R monoclonal antibodies or TNF-α inhibitors, may not be used. It should also not be used at the same time as live vaccines.

**Outcomes and Measures**

**Primary outcomes**

Changes in pulmonary CT score (7th day, 14th day or discharge time). The third-party imaging experts invited by the project team will carry out the blind evaluation.

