**Methods and analysis**

The experiment is divided into two stages. In the first stage, the open trial, 3 patients with COVID-19 are treated with ixekizumab, and the safety and efficacy are observed for 7 days. In the second stage, 40 patients with COVID-19 are randomly divided into two groups at 1:1 for 14 days. Patients with COVID-19 aged 18-75 with increased IL-6 levels will be enrolled. Inclusion was initiated in June 2020. The primary outcome is pulmonary CT score, and the secondary outcomes are pulmonary function, clinical symptoms, the incidence of admission to the ICU, the incidence of noninvasive ventilation, 14-day etiological mortality, length of hospitalization, and laboratory examination. The trial will provide data on the efficacy and safety of ixekizumab and antiviral therapy for patients with COVID-19.

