**Enrollment and follow-up**

Those who meet the enrollment criteria will enter the intervention:

On the 3rd day of enrollment, the following procedures will be performed: (1) record concomitant medication; (2) record adverse events; and (3) carry out CT examination.

On the 7th day (±1 day)), the following procedures will occur: (1) record the combined use of drugs; (2) record adverse events; (3) measure vital signs: respiratory rate, heart rate and blood pressure; (4) evaluate clinical symptoms: dyspnea score; (5) perform routine laboratory examination: routine blood, routine urine, liver and kidney function, blood glucose, electrolyte, troponin, hypersensitive CRP, procalcitonin, serum ferritin; (6) assess inflammation index (CRP, IL-6, TNF- α), infection index (routine blood tests, PCT) and immune function (T cell subsets); (7) analyze arterial blood gas: pH, PaO2, PaCO2 and oxygenation index; (8) perform HRCT examination and score; and (9) calculate APACHE II score.

Fourteen days after admission (±3 days) or discharge, (1) record the combined use of drugs; (2) monitor possible adverse reactions to ixekizumab; (3) check vital signs: respiratory rate, heart rate, blood pressure; (4) evaluate clinical symptom: dyspnea score; (5) perform routine laboratory examination: routine blood, routine urine, liver and kidney function, blood glucose, electrolyte, troponin, hypersensitive CRP, procalcitonin, serum ferritin; (6) assess inflammation index (CRP, IL-6, TNF-α), infection index (routine blood, PCT) and immune function (T cell subsets), and so on; (7) analyze arterial blood gas: pH, PaO2, PaCO2 and oxygenation index; and (8) perform HRCT examination and score; (9) APACHE Ⅱ score was calculated (Figure 1).

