**Treatment Protocols**

After the subjects sign the informed consent form, the researchers will complete the evaluation within 2 days.

The first phase: open design. Three subjects are enrolled in the same center. They are given ixekizumab and antiviral therapy (aerosol inhalation of α-interferon, lopinavir/ritonavir, chloroquine, ribavirin, or arbidol but not more than 3 types). The vital signs and changes in disease, inflammation indexes (CRP, IL-6, TNF-α) and infection indexes (routine blood tests) are monitored. Changes in PCT and immune function (T cell subsets) are detected. If there are no serious drug-related safety events in the patient's condition, the results of the first stage will be reported to the ethics committee for evaluation and approval, and the second phase of the study will be carried out.

In the second stage, 40 subjects are randomly divided into two groups at a 1:1 ratio. They are given ixekizumab and antiviral therapy (aerosol inhalation of α-interferon, lopinavir/ritonavir, chloroquine, ribavirin, or arbidol but not more than 3 types) or antiviral therapy alone. The course of treatment is 14 days. The vital signs, blood oxygen saturation, CT and other related indexes are followed up on days 0, 3, 7, and 14. The changes in inflammation indexes (CRP, IL-6, TNF-α), infection indexes (blood routine, PCT) and immune function (T cell subsets) and other indexes are monitored. The last follow-up is completed on the 14th day or early recovery and discharge (Figure 2).

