**Secondary outcomes**

1) Pulmonary function prognostic indicators: percentage of subjects reporting each severity level (on a 7-point scale) (https://clinicaltrials.gov/ct2/show/NCT04280705). The scale is the assessment of clinical status at the first evaluation on a specified study day. The indicators are as follows: (1) death; (2) admission due to invasive mechanical ventilation or extracorporeal membrane oxygenation (ECMO); (3) hospitalization with noninvasive ventilation or high-flow oxygen equipment; (4) hospitalization requiring oxygen inhalation; (5) hospitalization without oxygen inhalation; (6) hospital discharge with limited activity; and (7) no need to be hospitalized and activities are not restricted.

2) Clinical symptom relief time: Clinical symptom relief is defined as normal body temperature for >72 hours (without taking antipyretic drugs or glucocorticoids) and no conscious dyspnea or relief of dyspnea.

3) The incidence of admission to the ICU on the 3rd day, 7th day and 14th day;

4) The incidence of noninvasive ventilation on the 3rd, 7th and 14th days;

5) 14-day etiological mortality and 14-day all-cause mortality;

6) Length of hospitalization;

7) Changes in troponin, inflammation indexes (CRP, IL-6, TNF-α), infection indexes (blood routine, PCT) and immune function (T cell subsets)) on the 7th and 14th days.

8) The ratio of arterial partial pressure of oxygen (PaO2) to fraction of oxygen inhalation (FiO2) on the 3rd, 7th and 14th days.

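### The primary CT endpoint has no single designated time, and its late scan may be taken at discharge, so that scan's date depends on recovery; the visit clock is also inconsistent

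*Protocol*

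**What the plan says.** The Primary outcomes section defines the endpoint as "Changes in pulmonary CT score (7th day, 14th day or discharge time", read by blinded third-party imaging experts. It neither ranks nor combines the times. The abstract (Methods and analysis) says only "The primary outcome is pulmonary CT score", with no time and no mention of change.

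The scans are scheduled in two places:

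- **Enrollment and follow-up.** The first visit is described by "On the 3rd day of enrollment, the following procedures will be performed". The second is "On the 7th day (±1 day", with no origin of its own. The last, which includes a scored HRCT, is "Fourteen days after admission (±3 days) or discharge".
- **Treatment Protocols.** Here "CT and other related indexes are followed up on days 0, 3, 7, and 14", and "The last follow-up is completed on the 14th day or early recovery and discharge". Figure 2 shows the same four study days for both randomised arms.

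Two other statements bear on the point. Secondary outcomes lists "Length of hospitalization", so the protocol itself treats time to discharge as something to compare between arms. Sample Size Projections calls the study open and exploratory, and the control arm receives antiviral therapy alone.

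**The concern.** Three features of the endpoint are badly fixed.

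1. **No designated time.** Day 7 and the late scan stand side by side under the primary heading. If they disagree, the protocol does not say which one answers the primary question.
2. **A late scan whose date follows recovery.** A patient who leaves early is scanned at discharge, and one who stays is scanned around Day 14. If the arms differ in discharge timing, the late comparison sets different points of the disease course against each other. Only the CT reading is blinded. The decision to discharge, which sets the scan date, is made by staff who can know the arm, and blinded reading does not correct that.
3. **An inconsistent clock.** The visits are counted from enrolment, from admission and from Day 0 in different places. If admission means hospital admission, the nominal Day 14 falls at a different time since randomisation for each patient.

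At stake is what the primary result estimates. An analysis plan can choose between two recorded times. It cannot recover a Day 14 scan that was never taken because the patient had gone home.

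**Working it through.** **What can be reproduced.** The protocol gives no power calculation, alpha, SD or effect size. The only check on its own figures is the total: 3 open-label + 40 randomised = 43, which agrees. Everything below is illustrative and its assumptions are labelled.

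**Number of readings.** Primary outcomes alone could be read as two or three times. Enrollment and follow-up and Treatment Protocols both offer discharge as the alternative to Day 14, so the likeliest reading is two per patient: Day 7, and Day 14 or discharge.

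**Which readings can move.** The Day 7 window is 6 to 8. The final window is 14 ± 3 = 11 to 17, or discharge. Discharge on Days 11 to 13 stays inside that window if the days are counted from the same origin; discharge before Day 11 takes the scan outside it. Only the late reading clearly moves with discharge. Day 7 is affected only for patients who leave before it.

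**Size of a timing bias (assumed inputs).** Suppose both arms follow the same linear CT course and a fraction of one arm is scanned earlier.

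Bias in SD = slope per day × days earlier × fraction of the arm

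- Low: 0.05 × 2 × 0.5 = 0.05 SD
- High: 0.10 × 4 × 0.5 = 0.20 SD

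With 20 per arm and SD = 1, the standard error of the difference is √(2/20) = 0.316. A nominal two-sided 5% test of a true null then rejects with probability 5.3% at 0.05 SD and 9.7% at 0.20 SD.

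The sign is not fixed. If CT is improving and the ixekizumab arm leaves earlier, its scans come earlier in resolution and the bias runs against ixekizumab. If the control arm leaves earlier, or CT is still worsening, the direction reverses.

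**Two tests (assumed alpha and correlations).** With two-sided 5% at each time, the chance of at least one false positive is P(|Z1| > 1.96 or |Z2| > 1.96):

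| Correlation | Family-wise error |
|---|---|
| 0 (independent) | 1 − 0.95² = 9.75% |
| 0.5 | 9.1% |
| 0.7 | 8.3% |
| 0.9 | 7.0% |

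**The clock, if hospital admission is meant.** For a patient enrolled L days after admission, the final window in days since enrolment is (11 − L) to (17 − L). The protocol does not give L, so these values are assumed:

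| L | Final window since enrolment |
|---|---|
| 0 | 11 to 17 |
| 2 | 9 to 15 |
| 5 | 6 to 12 |

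At L = 5 the window overlaps Day 7 (6 to 8), provided Day 7 is itself counted from enrolment, which the text does not state.

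**The case against.** The strongest reply is that this is a pilot with no estimated sample size, no stated alpha and no success rule, so error-rate arguments apply a confirmatory standard. That stands. A reader might infer that a win at either time would be declared a primary success with an inflated false-positive rate. The protocol states no such rule, and the analysis plan, which is not at hand, may settle multiplicity. The 7% to 9% is therefore illustrative.

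A reader might also infer that Day 14 is definitely counted from hospital admission. The phrase occurs once, under a heading about enrolment, and may mean admission to the study; Treatment Protocols and Figure 2 use study days. The documents support an inconsistency to reconcile, and no more.

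Nor are all the primary scan dates outcome-dependent: Day 7 has a fixed window. The timing bias rests wholly on assumed inputs. At its low end it is negligible, and part of the shift lies within the permitted ±3 days.

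It is also tempting to fault the endpoint for being a change score without baseline adjustment. The protocol fixes no model, and a change score can be analysed with baseline as a covariate. Adjustment would be a sensible addition, but its absence here is not an error.

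The reply does not remove the core. An exploratory trial still needs to say what its primary outcome is. The discharge substitution is a stated rule about when scans are taken, and later analysis cannot fully repair it.

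**Conclusion.** The point holds in limited form and should be fixed. No primary time is designated, and the late primary scan may be taken at a date set by recovery in a trial where treating staff can know the arm. The visit origins also conflict.

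The direction and size of any bias are unknown. The 0.05 to 0.20 SD range depends on the assumed slope, shift and fraction. For scale, 20 per arm detects about 0.89 SD with 80% power at an assumed two-sided 5%: (1.96 + 0.84) × 0.316. The illustrated bias is well below that. The main defect is an endpoint that is not uniquely defined, rather than a demonstrated error of known size.

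**What to change.** - **Name one primary time**, counted from randomisation, with its window. Do not let a discharge scan replace it.
- **Make the other time secondary**, and record the actual days since randomisation for every scan.
- **Use one origin for all visits.** Bring the abstract, Enrollment and follow-up, Treatment Protocols, Primary outcomes and Figure 2 into line, and state what admission was meant to be.

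Either time is acceptable. Day 7 (±1) is cheapest, because the scored scan is already scheduled and most of the change is wording. It needs a scan within the window for any patient discharged before it, or a statement of how such patients are handled. Its downside is that the two-week effect becomes secondary. Day 14 keeps the two-week effect as primary but costs a return visit for discharged patients.

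As an optional addition, the chosen time can be compared with adjustment for baseline CT score, which is already collected.

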**Secondary outcomes**

1) Pulmonary function prognostic indicators: percentage of subjects reporting each severity level (on a 7-point scale) (https://clinicaltrials.gov/ct2/show/NCT04280705). The scale is the assessment of clinical status at the first evaluation on a specified study day. The indicators are as follows: (1) death; (2) admission due to invasive mechanical ventilation or extracorporeal membrane oxygenation (ECMO); (3) hospitalization with noninvasive ventilation or high-flow oxygen equipment; (4) hospitalization requiring oxygen inhalation; (5) hospitalization without oxygen inhalation; (6) hospital discharge with limited activity; and (7) no need to be hospitalized and activities are not restricted.

2) Clinical symptom relief time: Clinical symptom relief is defined as normal body temperature for >72 hours (without taking antipyretic drugs or glucocorticoids) and no conscious dyspnea or relief of dyspnea.

3) The incidence of admission to the ICU on the 3rd day, 7th day and 14th day;

4) The incidence of noninvasive ventilation on the 3rd, 7th and 14th days;

5) 14-day etiological mortality and 14-day all-cause mortality;

6) Length of hospitalization;

7) Changes in troponin, inflammation indexes (CRP, IL-6, TNF-α), infection indexes (blood routine, PCT) and immune function (T cell subsets)) on the 7th and 14th days.

8) The ratio of arterial partial pressure of oxygen (PaO2) to fraction of oxygen inhalation (FiO2) on the 3rd, 7th and 14th days.

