**Eligibility Criteria**

The inclusion criteria for the trial are as follows: the age is 18-75 years old, regardless of sex; COVID-19 will be diagnosed by RT-PCR or gene sequencing; the clinical types are common type (including severe high-risk factors) (multiple lesions of both lungs, or lung imaging showing that the lesion progressed more than 50% within 24 to 48 hours) and severe type; an increase in IL-6 levels; and the patient voluntarily signing the informed consent form.

The exclusion criteria for the trial are as follows: severe new pneumonia infection with one of the following conditions: respiratory failure requiring mechanical ventilation, shock, ICU monitoring and treatment with other organ failure; allergy to ixekizumab or antiviral drugs; ALT/AST>5 times the ULN, neutrophils<0.5 × 10^9/^L, or platelet less than 50 × 10^9^/L; patients with impaired renal function: serum creatinine ≥2 mg/dl (176 μmol/l); complications with severe underlying diseases or a life expectancy of less than 3 months; patients with active hepatitis, definite severe bacterial or fungal infections, tuberculosis infection, or HIV infection; malignant tumors, such as lymphoproliferative diseases; active Crohn's disease; pregnant or lactating women; participation in other intervention clinical trials in the past 3 months; or other situations in which the researchers believe that it is not appropriate to join the group.

The termination standards for the trial are as follows: allergy to research drugs; judgment of the researchers that it is necessary to terminate the study ahead of time because continuing to participate in the study may bring unacceptable risks to the subjects' health based on the occurrence of serious adverse events, or the subjects are unwilling to continue to participate in the study because of the adverse events; the observation of the curative effect was affected by other diseases such as stroke in the trial; or the ethics committee or regulatory body requested that the study be suspended.

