**Baseline Procedures**

The following assessments must be completed during the screening period: medical history, occupational history, drug history, hobbies and smoking history; vital signs: respiratory rate, heart rate, and blood pressure; clinical symptom evaluation: dyspnea score; routine laboratory examination: routine blood tests, routine urine tests, liver and kidney function, blood glucose, electrolytes, troponin, serum ferritin, CRP, IL-6, TNF-α, PCT and T cell subsets; arterial blood gas analysis: pH, PaO2, PaCO2 and oxygenation index; routine electrocardiographic examination (ECG); chest high-resolution CT (HRCT) examination and score; and APACHE II score.

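### Symptom relief is defined as a state that a patient with neither fever nor dyspnea at entry already meets, or meets by default just after Day 3, and its dyspnea-relief branch has no threshold

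*Protocol*

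**What the plan says.** **Outcome.** Item 2 under Secondary outcomes reads: "Clinical symptom relief is defined as normal body temperature for >72 hours (without taking antipyretic drugs or glucocorticoids) and no conscious dyspnea or relief of" (last word, naming the symptom, omitted). It does not say who is at risk of the event, when the clock starts, or how to score a patient who already meets the definition.

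**Entry.** Under Eligibility Criteria, "COVID-19 will be diagnosed by RT-PCR or gene sequencing". The common type is qualified by imaging findings ("multiple lesions of both lungs, or lung imaging showing that the lesion progressed more than 50% within 24 to 48 hours"). The other eligible type and the cytokine criterion follow: "and severe type; an increase in IL-6 levels". The severe type is not defined. Neither fever nor dyspnea is listed as a condition of entry.

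**Measurement.** Baseline Procedures list "clinical symptom evaluation: dyspnea score" and "vital signs: respiratory rate, heart rate, and blood pressure". Temperature is not among the vital signs there, nor at the visits under Enrollment and follow-up. That section schedules the dyspnea score at Day 7 and at Day 14 or discharge, but not at Day 3.

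**Blinding and allocation.** Treatment Protocols randomise 40 patients 1:1 to ixekizumab plus antivirals or to antivirals alone, with no placebo. The Randomization section provides blinded reading for CT only and states no stratification by baseline symptoms.

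**The concern.** A time-to-relief outcome is informative when patients start with something to be relieved of. Here the dyspnea part, "no conscious dyspnea or relief of dyspnea", is met by never having had the symptom, and the temperature part is met by never having had fever. Patients with neither contribute an event whose timing is set mainly by the definition. They blur a real difference between arms. In a trial of this size, an uneven split of them can also move one relief curve without any drug effect.

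The second weakness is separate. The relief branch sets no size of improvement, although a dyspnea score is collected. Any easing that a patient reports could count, and patient and site staff know the treatment.

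**Working it through.** **No plan figure to reproduce.** The protocol gives no effect size, event rate, alpha or power for this outcome and says that the sample size was not statistically estimated.

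**Step 1: apply the definition to a permitted patient.** Take a common-type patient with RT-PCR confirmation, lesions in both lungs, raised IL-6, no fever and no breathlessness. No stated entry criterion excludes this patient.
- Dyspnea part: met on the first day.
- Temperature part: met on the first day if a run of more than 72 hours off antipyretics and glucocorticoids has already been documented. If the run starts at enrolment, it is met just after Day 3 (72 h / 24 h = 3 days), provided that the patient stays well.

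**Step 2: chance imbalance.** Inputs: 20 per arm (40 / 2) from the protocol; a symptom-free share f, which is assumed. Let A and B be the symptom-free numbers in the two arms, independent Binomial(20, f).

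SD of the difference = √(2 × 20 × f × (1 − f)). At f = 20% this is √6.4 = 2.53. A gap of 4 patients is 4/20 = 20 percentage points. P(|A − B| ≥ 4) is the sum of P(A = a) × P(B = b) over all pairs at least 4 apart.

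| Assumed f | Expected per arm | SD of difference | P(gap of 4 or more) |
|---|---|---|---|
| 10% | 2 | 1.90 | 6% |
| 20% | 4 | 2.53 | 16% |
| 30% | 6 | 2.90 | 23% |
| 40% | 8 | 3.10 | 26% |

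**Step 3: dilution and false positives.** Log-rank simulation, 2,000 runs per setting. Assumptions: control median 7 days, relief-rate ratio 2 among symptomatic patients, censoring at Day 14, symptom-free patients scored at Day 0.

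| Assumed f | Power | Mean difference in medians (days) |
|---|---|---|
| 0% | 51% | 3.7 |
| 10% | 41% | 3.0 |
| 20% | 36% | 2.6 |
| 30% | 29% | 1.8 |

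Scoring them at Day 3, with all other relief times moved to after Day 3, gives nearly the same pattern. Across all settings with no treatment effect, the rejection rate was 4.6% to 6.2%, close to the nominal 5%.

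**Step 4: what restriction buys.** The 51% row assumes 20 symptomatic patients per arm, but restriction removes patients: at f = 20%, about 16 per arm remain (20 × 0.8). On the same assumptions, a rerun at f = 20% gives about 35% power with everyone included and 42% after restriction. With symptom-free events at Day 3 and the other times left unshifted, the figures are about 40% and 43%.

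**The case against.** **The entry premise is not watertight.** Patients enter by clinical type, and the protocol defines neither type fully. The severe type may often bring dyspnea. This stands as a limit on how large the share is. It does not remove the point, because no symptom is stated as a condition and the common type is described by imaging.

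**A reader might infer that these patients all count as relieved at time zero.** That holds only where a fever-free run of more than 72 hours before enrolment is documented. The listed procedures do not include temperature, so they would not document one. Otherwise the event falls just after Day 3.

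**A reader might infer that they carry no information at all.** This is too strong. If the run starts at enrolment, a patient with progressing lesions could become febrile or breathless first, so staying well could reflect treatment.

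**A reader might infer a biased comparison.** The documents do not support that. Randomisation balances the symptom-free share in expectation, and the simulated false-positive rate is unaffected. Chance imbalance at 20 per arm applies to any prognostic factor.

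**Larger imbalance figures are possible but sit at the high end.** Fixing the total at 8, 12 or 16 of 40 gives 24%, 30% or 33% for a gap of 4 or more. With an even total the gap can only be even, so those figures also cover a gap of 3 or more.

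**The clock start and the handling of these patients could be left to a SAP.** That is fair for details. The definition itself is in the protocol, however, and baseline fever status cannot be recovered if temperature is not recorded.

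**The direction of any bias from the relief branch is presumed.** This is accepted: exposure to expectation bias can be read from the design, but its direction and size cannot.

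**Conclusion.** The point holds in a limited form. As written, the outcome scores patients with neither symptom at entry as relieved, either at once or by default just after Day 3. The harm is dilution and chance imbalance. The size depends on a share that the protocol does not give. Over an assumed 10% to 40%, a gap of 20 percentage points or more between arms has a chance of about 6% to 26%. The power figures also rest on an assumed control median and rate ratio, and the gain from restricting the analysis is modest: about 3 to 7 percentage points at a 20% share.

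The missing threshold for dyspnea relief is a separate weakness in an open-label comparison, with no size that can be calculated from the protocol.

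This is one of eight secondary outcomes in an exploratory trial. The primary CT outcome, which is read blind, is not affected. The change is worth making because it is cheap, but the point does not threaten the trial's main result.

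**What to change.** - Analyse outcome 2 in patients with fever or dyspnea at randomisation, and count time from randomisation.
- Report the number with neither symptom at baseline, by arm.
- Tie dyspnea relief to a pre-stated change on the existing dyspnea score, judged at its scheduled assessments (baseline, Day 7, and Day 14 or discharge). A requirement that the change be held for 72 hours could not be met from data collected on that schedule.
- Add body temperature to the vital signs recorded at baseline and during follow-up.

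The cost is more than wording. The denominator for this one outcome shrinks, and temperature has to be added to the recorded items, although the present definition cannot be applied without it anyway. Using the scheduled scores also means that dyspnea relief is dated only to those visits. No change to treatment, entry or the primary outcome is needed.

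### Clinical symptom relief can be scored for an afebrile patient whose dyspnea eased only after escalation to noninvasive ventilation or high-flow oxygen

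*Protocol*

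**What the plan says.** The Protocol, Secondary outcomes, item 2, fixes the endpoint in two halves, temperature and dyspnea: "normal body temperature for >72 hours (without taking antipyretic drugs or glucocorticoids) and no conscious dyspnea or relief of dyspnea".

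The same section treats a rise in respiratory support as a poor outcome.

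- Item 1 is a 7-point scale on which 1 is death. Level 2 is "admission due to invasive mechanical ventilation or extracorporeal membrane oxygenation (ECMO"), and level 3 is "hospitalization with noninvasive ventilation or high-flow oxygen equipment". Oxygen without these is level 4, and hospital stay without oxygen is level 5.
- Item 4 is "The incidence of noninvasive ventilation on the 3rd, 7th and 14th days".

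Eligibility Criteria exclude severe cases with "respiratory failure requiring mechanical ventilation, shock, ICU monitoring and treatment with other organ failure", but only at entry. On steroids, the section on permissible combinations says: "If the condition requires short-term use of glucocorticoids, it is accurately recorded".

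**The concern.** The authors saw that another treatment can mask a symptom and protected the temperature half against it. They gave the dyspnea half no such protection, although oxygen and ventilatory support act directly on breathlessness. A patient can then enter the relief count because support was stepped up, which the neighbouring outcomes count as deterioration.

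Two things are at stake. Individual patients may be misclassified, so that item 2 disagrees with items 1 and 4 about the same person. And if one arm is escalated more often than the other, that arm collects more false relief events. If the drug prevents escalation, the surplus falls in the control arm and shrinks the difference the trial is looking for. Only the CT reading is described as blinded, so reported dyspnea and the decision to escalate are open to knowledge of treatment.

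**Working it through.** **1. Does the rule admit the patient?** Let T = afebrile for more than 72 hours off antipyretics and glucocorticoids, N = no conscious dyspnea, R = relief of dyspnea. The wording can be grouped as T and (N or R), the natural reading, or as (T and N) or R.

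| Patient | T and (N or R) | (T and N) or R |
|---|---|---|
| Noninvasive ventilation, dyspnea eased, T met | relief | relief |
| Noninvasive ventilation, dyspnea eased, on glucocorticoids | not relief | relief |
| Noninvasive ventilation, dyspnea eased, febrile | not relief | relief |
| Intubated and sedated, taken as N, T met | relief | relief |
| Intubated and sedated, febrile | not relief | not relief |

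The first row qualifies under both groupings. High-flow oxygen behaves in the same way.

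**2. Does another section close the gap?** The ventilation exclusion applies at entry. Later ventilation is not in itself a termination or exit reason, so these patients stay in follow-up. The cointervention sections say nothing about respiratory support and scoring. A dyspnea score is taken at screening, day 7 and day 14 or discharge, but item 2 does not refer to it. No section supplies the missing condition.

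**3. One record against three outcomes (days chosen for illustration).** A patient enters on oxygen (level 4), is afebrile from Day 1 off antipyretics and glucocorticoids, starts noninvasive ventilation on Day 4 and breathes more easily on Day 5. By Day 5 the afebrile run is 4 × 24 = 96 hours, which exceeds 72.

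- Item 2: relief can be declared on Day 5.
- Item 1: level 4 has become level 3, which is worse.
- Item 4: counted if ventilation continues to day 7.

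**4. Possible size.** The protocol states no escalation or recovery rates, so every rate here is an assumption. Take 70% true recovery by Day 14 among patients never escalated, escalation of 30% in controls and 10% with ixekizumab, no true recovery by Day 14 among escalated patients, and a share *f* of escalated patients falsely scored as relieved, equal in both arms.

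Proportion relieved = (1 − escalation) × 0.70 + escalation × *f*

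- True difference (*f* = 0): 0.90 × 0.70 − 0.70 × 0.70 = 0.63 − 0.49 = 0.14.
- Difference as scored: 0.14 + (0.10 − 0.30) × *f* = 0.14 − 0.20*f*.

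| *f* | Difference as scored | Dilution | False events per 20 controls | False events per 20 on ixekizumab |
|---|---|---|---|---|
| 0.25 | +9 points | 5 points | 20 × 0.30 × 0.25 = 1.5 | 20 × 0.10 × 0.25 = 0.5 |
| 0.50 | +4 points | 10 points | 3.0 | 1.0 |
| 0.75 | −1 point | 15 points | 4.5 | 1.5 |

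If 25% of escalated patients truly recover by Day 14, the true difference is itself 0.14 − 0.20 × 0.25 = 0.09. The dilution per unit of false share stays at 0.20.

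With escalation of 20% in both arms, each arm has 20 × 0.20 × *f* = 1, 2 or 3 false events. The same amount is added to both arms, so the difference does not change.

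**The case against.** **The temperature half already screens.** This stands. A reader might infer that escalated patients in general are scored as relieved. On the natural reading, those who are febrile, on antipyretics or on glucocorticoids are not, and glucocorticoids are permitted. The endpoint can be reached by some escalated patients, and the text supports no more than that.

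**Sedated patients.** A reader might infer that intubation counts as relief. That needs a literal reading of no conscious dyspnea for someone who cannot report. The natural view is that such a patient cannot be assessed. The noninvasive ventilation case does not depend on this reading.

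**Relief compared with what?** Item 2 gives no comparator or threshold. If relief is judged against the screening dyspnea score, a patient who worsened and then eased on support need not qualify. That narrows the problem but does not remove it, because support can also bring dyspnea below its entry level.

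**Symptoms and support are different constructs.** Items 1, 3, 4 and 5 would still show the deterioration. True, but they do not correct item 2, which would be reported as relief.

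**Size.** The figures are all assumed, and they describe a proportion by Day 14 while the endpoint is a time. A reader might infer that a real benefit would be reversed. That takes *f* = 0.75, and even then gives −1 point, or 0.01 × 20 = 0.2 of a patient. The standard error of 63% versus 49% with 20 per arm is √(0.63 × 0.37/20 + 0.49 × 0.51/20) = 0.155, so the assumed dilution of 5 to 15 points lies within one standard error. Nor do the documents show that escalation will differ between arms.

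**Leave it to the statistical analysis plan.** Handling of deaths and censoring may well sit there. But the protocol does not leave this definition open: it states a rule, and the rule as stated admits the patient.

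**Conclusion.** The point holds in a limited form. As written, an afebrile patient off antipyretics and glucocorticoids whose dyspnea eased only after escalation to noninvasive ventilation or high-flow oxygen can be scored as relieved. Item 1 scores that patient as worse, and item 4 counts the noninvasive ventilation. This follows from the wording and needs no assumed rate.

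The effect on the comparison is conditional. If escalation differs between arms, the difference is diluted by the escalation gap times the false share, which is 5 to 15 points under the assumed 20-point gap. With equal escalation and an equal false share there is misclassification without bias in the difference. The documents give no rates, so the actual size is unknown, and neither reversal nor imbalance between arms can be asserted as fact.

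This is one of eight secondary items in an exploratory comparison of 40 patients, and the primary CT outcome is untouched. The definition is still worth correcting because the repair is small.

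**What to change.** Add to item 2 that relief counts only on a day when both of these hold: the patient is at level 4 or better on the protocol's 7-point scale, and respiratory support is no higher than at enrolment. A patient at levels 1 to 3, or on more support than at enrolment, is not relieved until both conditions and the existing temperature and dyspnea rule are met.

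Both conditions are needed. A patient enrolled at level 5 who falls to level 3 and returns to level 4 passes on level alone, but is still on more support than at entry.

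Cost: one sentence in the endpoint definition and slightly fewer relief events. The support level must also be recorded on the day relief is declared. The scale is read on specified study days and follow-up falls on days 0, 3, 7 and 14, which is too sparse for a time-to-relief endpoint. The change affects only how the outcome is scored, not how patients are managed.
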